## Abstract

Background/Objectives: Depression is a prevalent and debilitating illness that significantly affects psychological and physical well-being. Apart from conventional therapies such as psychotherapy and medication, individuals with depression often lack opportunities for activities that are generally perceived as enjoyable, such as music, meditation, and arts, which have demonstrated therapeutic effectiveness. TaKeTiNa music therapy has been employed as a therapeutic intervention for more than two decades. However, there is a notable absence of well-designed clinical trials investigating its antidepressant effects, a gap we aim to address in our current study. Furthermore, shifts in the progression of depression may manifest both psychologically, by influencing emotional states, and physiologically, by leading to alterations in lipid and sphingolipid metabolism, cortisol levels, and immune system function. Our study seeks to analyze the impact of TaKeTiNa music therapy on both levels. Methods: This is a prospective monocentric randomized waitlist-controlled clinical trial. It investigates the influence of TaKeTiNa music therapy on patients with major depression in an outpatient setting. Therefore, interested persons are randomly assigned to two groups, an intervention group or a control group, after completing a screening procedure. The intervention group starts with an eight-week TaKeTiNa music therapy intervention. The waiting group receives the same therapy program after completing the follow-up period. Blood and saliva sampling as well as responses to questionnaires are obtained at specific time points. Discussion: Our study investigates the effects of TaKeTiNa music therapy, a non-pharmacological antidepressant treatment option, on depressive symptoms. We also address functional and causal immunological changes; hormonal changes, such as changes in cortisol levels; and metabolic changes, such as changes in serum lipids and sphingolipids, during the course of depression. We expect that this study will provide evidence to expand the range of treatment options available for depression.

## 1. Background

Depression is one of the most common diseases, with a lifetime risk of up to 20% [1]. It leads not only to psychological but also to physical and social impairments [2,3,4]. Treatment reduces the duration of the disease. Depending on the severity and type of the depressive illness, various forms of treatment are recommended, primarily medication and psychotherapy [1]. However, one-third of patients do not respond to conventional pharmacotherapy, highlighting the need for additional, evidence-based therapies via a multimodal approach. The treatment landscape encompasses non-pharmacological modalities, such as cognitive behavioral therapy [5], mindfulness-based interventions [6], art therapy [7], physical exercise [8], including bouldering (climbing without rope in moderate heights) [9], and the implementation of mental models [9], each offering promising avenues for symptom alleviation and improved quality of life.

In the last two decades, there has been increasing scientific interest in music therapy for mental conditions. Music and music therapy have positive and reproducible effects in different areas, e.g., dementia, insomnia, and anxiety [10,11,12,13,14], and may also improve the tolerability of therapies such as listening to music during intranasal (es)ketamine application [15]. Although there are indications of positive effects on depression [10], these effects appear to be short-term and lack sufficient clinical impact. One reason could be that the studies are usually conducted with very narrow, specific procedures. Interventions such as merely passively listening to classical music or solely rhythmically playing on a drum leave many potential aspects of music therapy untapped, especially because their combination may improve many characteristic symptoms of depression.

TaKeTiNa is a therapeutic modality that harnesses the power of rhythm and movement to foster personal development and overall well-being. Originating from the innovative work of the Austrian musician Reinhard Flatischler, TaKeTiNa music therapy integrates group rhythmic exercises, vocalizations, and bodily movements to induce states of mindfulness, relaxation, and interconnectedness. Participants partake in repetitive rhythmic patterns involving hands, feet, and voice, often in a communal setting, with the goal of facilitating harmonious synchronization of body, mind, and spirit through rhythmic exploration. The name “TaKeTiNa” is emblematic of the rhythmic syllables central to the practice, including “Ta”, “Ke”, “Ti”, and “Na”, which are vocalized and clapped in precise configurations during TaKeTiNa sessions, contributing to its therapeutic impact. Each member of the group is needed for the synchronization of the whole group. Once the group is synchronized, the therapist introduces musical elements in varying degrees of difficulty to let the participants experience their psychological and bodily reactions to outer demands in an immediate way. Through this process, participants become more mindful of their reactions to the outer world. Moreover, through phases of challenging and relaxing elements introduced by the therapist, they learn to deal appropriately with phases of active focus and active relaxation. In this way, TaKeTiNa helps to relearn a healthy response to the changing outer world and an awareness of the inner world while addressing many symptoms of depression, such as social isolation, lack of purpose, adynamia, lack of concentration, and physical inactivity, in therapy sessions.

In the past few years, numerous studies have shown that—among other neurobiological mechanisms of depression [16]—the immune system is involved in the development and course of depression, as well as the therapy resistance of patients [17]. The high number of therapy-refractory patients has led to the need for alternative treatment strategies. The levels of inflammatory cytokines produced by the adaptive immune system, such as tumor necrosis factor (TNF)-alpha, interleukin (IL)-1β, and IL-6, are elevated in patients with depression, whereas the levels of anti-inflammatory cytokines, such as IL-4, IL-10, and transforming growth factor (TGF)-ß, are decreased [18]. Inflammation is assumed to impact neurotransmitter systems and thereby cause depressive symptoms. High inflammation in patients with depression has been shown to be associated with metabolic alterations [19]. Moreover, blocking inflammatory cytokines has been reported to decrease depressive symptoms and reduces the cholesterol concentration in patients with elevated inflammatory markers [19,20]. Many depressed patients exhibit glucocorticoid resistance due to reduced function of the glucocorticoid receptor, which is assumed to be relevant for increased inflammation [21]. Additionally, major depressive disorder, cardiovascular disease, and type 2 diabetes share immune inflammatory alterations [22] and are linked to dyslipidemia. Dyslipidemia, characterized by elevated low-density lipoprotein (LDL) cholesterol, can be associated with chronic cortisol exposure [23]. Prolonged stress and associated dyslipidemia can have a negative impact on health [24]. Heart rate variability (HRV) has been shown to be a sensitive marker for the psychological stress response [25] as well as for individuals with depression during stress [26]. Therefore, the changes described above could be assumed to be linked to altered function of the hypothalamic–pituitary–adrenal axis. In our previous work, we demonstrated that serum lipid levels are associated with depression per se, depression severity, and the prospective course of the disease. We were able to establish the serum lipid levels, particularly the serum LDL concentration, as a biomarker to predict the prospective 20-day short-term course of depression [27]. Treatment with antidepressants had no strong impact on the association between lipid levels and depression severity in our cohort. Thus, independent of antidepressant therapy, immune processes and lipid metabolism might influence each other and lipid metabolism might be an important player in therapeutic resistance in patients with depression [28]. Using the ratio of different immune cells, such as Th1, Th2, and Th17 cells, as surrogate markers, we might be able to better predict the severity of depression and the probable response to therapy. Dysregulation of sphingolipids, a special class of bioactive lipids that are major constituents of membranes, in combination with their metabolizing enzymes related to central ceramide [29,30], has recently gained attention for its role in the pathogenesis and treatment of anxiety and depression in animal models [31,32] and human studies [33,34]. Blood ceramide levels are significantly increased in depressed patients [35,36,37]. We previously showed that the activity of serum acid sphingomyelinase activity, which catalyzes the generation of ceramide, can predict the prospective course of patients [38]. Here, we aim to investigate the interaction between the course of depression after non-pharmacological treatment and serum lipid levels and inflammatory mechanisms.

The goal of this study, which includes a naturalistic cohort, is threefold. First, we hypothesize that participants in the intervention group (IG) receiving 8 weeks of TaKeTiNa music therapy will experience a pre–post decrease in depression. Second, we assess a wide range of potential mediating and moderating factors, such as anxiety, resilience, and mindfulness. Third, we analyze the physiological factor HRV and blood biomarkers, such as serum lipid levels, sphingolipid and corresponding enzyme levels, cytokine levels and immune cell profiles, in relation to changes in depression severity.

## 2. Materials and Methods

### 2.1. Study Design

This is a prospective monocentric randomized waitlist-controlled clinical trial investigating the influence of TaKeTiNa music therapy for patients with major depression in an outpatient group setting on the primary and secondary outcomes of depression.

Participants are randomized to either the intervention group (IG) or control group (CG). After the end of the follow-up period, the CG is offered the intervention. To reach the target numbers of participants, there are two consecutive rounds each of intervention (IG1 and IG2) and control (CG1 and CG2) groups. The combined IG1 and IG2 groups are defined as patients who start TaKeTiNa treatment. The combined CG1 and CG2 groups include patients who start with a waitlist (Figure 1).

### 2.2. Objectives

With this study, we aim:To investigate the effects of TaKeTiNa music therapy on depression scores and blood-based parameters, especially LDL cholesterol, in patients with depression.To identify the modifying factors of therapy response, such as anxiety, resilience, and mindfulness.To investigate the relationships between depression-related physiological markers, such as HRV, and biological markers, including immune-system-based biomarkers, lipids, and sphingolipids.

Primary and secondary hypotheses:

Our hypotheses are as follows:TaKeTiNa results in a significant decrease in depression severity due to the intervention (from before visit 1 to visit 3 after 8 weeks of therapy) (combined IG1 and IG2 groups).TaKeTiNa results in significantly stronger pre-to-postintervention depression severity decrease (visit 1 to visit 3) in the IG1/IG2 group compared to the CG1/CG2 group.

Further hypotheses:The antidepressive effect of TaKeTiNa postintervention is stable over eight weeks (from visit 3 to visit 4).Depressed patients with higher LDL cholesterol also show higher cortisol levels.A higher LDL cholesterol level and higher acid sphingomyelinase activity in depressed patients predict greater symptom reduction with (additional) non-pharmacological treatment strategies such as TaKeTiNa.TaKeTiNa significantly reduces salivary cortisol levels in depressed patients.TaKeTiNa significantly reduces proinflammatory cytokines in depressed patients.The HRV at baseline is inversely correlated with the depression severity score and improves during treatment.

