### 2.3. Participants

The study is conducted in the city of Erlangen, Germany. Adult outpatient participants with major depression are recruited. The patients are informed via flyers and posters at the hospital as well as via newspaper entries. Study email and phone numbers are provided where interested parties can ask questions and sign up for the study prescreening. A weblink for the prescreening is then sent out to test for eligibility criteria including Patient Health Questionnaire (PHQ-9) as a multipurpose instrument to assess depression severity. Interested persons who prefer a telephone pre-screening to the online link can also choose to do so. If eligible, potential participants are contacted and invited to an in-person meeting with a physician to receive explanations about the study content and procedures and are asked to sign the informed consent form. Participants continue to receive treatment as usual offered by their psychotherapist or medical doctor.

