### 2.5. Sample Size

A sample size of 120 was calculated for the primary hypothesis: TaKeTiNa results in a significant pre-to-postintervention decrease in depression severity (combined IG1 and IG2 groups). According to the sample size calculation (one-tailed *t* test, difference between two dependent means, significance level 0.05, power 0.80, G*Power 3.1.9.7, downloaded 2020), 52 participants in the intervention group are sufficient to demonstrate a Cohen’s d of 0.35 and thus even a small effect size. Anticipating a dropout rate of 15% and striving for equal group sizes, our study aims to enroll a total of 120 participants who are evenly distributed between the intervention and control groups.

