### 2.6. Randomization/Blinding

Participants are assigned a unique, sequential three-digit number code based on their screening order, with the assignment list securely destroyed after data collection. This proposed study is designed as a wait-list-controlled randomized group pilot study in which patients are randomly allocated to the IG and CG. This randomization process involves sorting participants by sex and age and then alternately assigning them to either the IG or CG to ensure nearly age-matched groups. Raters for rater based interviews are blinded.

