### 2.10. Safety

For each participant, there will be three appointments for blood samples (approximately 30–40 mL of blood, i.e., approximately 100 mL in total in four months) and four time points to fill out the online questionnaires. Similar to mindfulness-based practices such as meditation, TaKeTiNa leads to increased awareness. In some cases, such practices can lead to a stronger experience of difficult feelings and thereby exacerbate psychological problems. If study subjects experience an increase in psychological symptoms, they can contact our emergency unit at any time and immediate psychiatric help will be offered. Therefore, we conclude that the potential benefits outweigh the potential risks. People who score more than four on PHQ-9 are asked to call our outpatient care unit for an appointment. If participants show suicidal thoughts in the screening interview (conducted by a medical doctor), treatment options will be discussed with the patients and clinical care will be offered. At least one medical doctor experienced in psychiatry is always available for the duration of the TaKeTiNa units.

Criteria for withdrawal from the study: Each participant has the possibility to withdraw the informed consent. We exclude patients who report suicidal tendencies, severe somatic illness, or admission to the hospital during participation.

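### The primary hypothesis is a causally worded but uncontrolled change within the intervention arm; the comparison with the waitlist ranks only second and was not used for sizing

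*Protocol article*

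**What the plan says.** Section 2.1 sets out the design: "This is a prospective monocentric randomized waitlist-controlled clinical trial".

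Section 2.2 lists two hypotheses under a joint heading for primary and secondary, without saying which is which. The first concerns the combined intervention groups only, from visit 1 to visit 3: "TaKeTiNa results in a significant decrease in depression severity due to the intervention". The second is the controlled comparison over the same visits: "TaKeTiNa results in significantly stronger pre-to-postintervention depression severity decrease (visit 1 to visit 3) in the IG1/IG2 group compared to the CG1/CG2 group".

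Section 2.5 settles the ranking. The sample size of 120 was "calculated for the primary hypothesis: TaKeTiNa results in a significant pre-to-postintervention decrease in depression severity (combined IG1 and IG2 groups". The calculation is for a one-tailed t test of two dependent means, with alpha 0.05, power 0.80, d = 0.35 and 52 participants in the intervention group. The control arm's size follows from the wish to have arms of the same size, after an allowance for 15% dropout. The last paragraph of Section 1 agrees: the first goal is a pre-post fall in the intervention group.

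Section 2.3 adds: "Participants continue to receive treatment as usual offered by their psychotherapist or medical doctor".

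**The concern.** A paired test in one arm answers whether patients were better at visit 3 than at visit 1. It cannot say why. Continuing usual care, the natural course of a depressive episode and regression to the mean can all lower HAMD-17 over eight weeks without any contribution from the therapy. A concurrent control removes these influences. This trial enrols such a control but leaves it out of the primary test.

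At stake is the trial's main claim. The primary hypothesis attributes the decrease to the therapy, and the test attached to it cannot support that attribution. The comparison that could support it has a lower rank and no stated power.

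**Working it through.** **Inputs.** From Section 2.5: paired t test, one-tailed, alpha 0.05, power 0.80, d = 0.35, n = 52 in the intervention group, 15% dropout, 120 in total, equal arms. Not in the document and therefore assumed: the improvement without TaKeTiNa, the between-arm difference, and the correlation r between HAMD-17 at visits 1 and 3. For a paired test, d is the mean change divided by the SD of change.

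**Step 1: the plan's own figure.** Power = P(T > t(0.95, n-1)), where T is noncentral t with noncentrality d√n. At n = 52 the noncentrality is 0.35 × √52 = 2.52 and the power is 0.801. At n = 51 it is 0.794. So 52 reproduces. The total also follows: 52 × 1.15 = 59.8, rounded to 60 per arm, or 120.

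**Step 2: the primary test when the therapy adds nothing.** Let both arms improve by the same δ, in SD of change. The test sees only the intervention arm, so the formula of step 1 applies with δ in place of d.

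| Common improvement δ | δ√52 | P(primary test positive) |
|---|---|---|
| 0.10 | 0.72 | 17.5% |
| 0.20 | 1.44 | 41% |
| 0.35 | 2.52 | 80% |
| 0.50 | 3.61 | 97% |

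If the shared improvement equals the effect used for sizing, a therapy that adds nothing gives a positive primary test as often as the stated power. In a simulation of 100,000 trials with 52 per arm and equal improvement in both, the primary test was positive while a one-sided between-arm test was not in about 75% of trials at δ = 0.35 and 92% at δ = 0.50.

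**Step 3: power of the second hypothesis at the planned size.** Assume that 0.35 SD of change carries over to the between-arm difference in change. With 52 completers per arm the noncentrality is 0.35 × √(52/2) = 1.78.

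| | One-sided 0.05 | Two-sided 0.05 |
|---|---|---|
| Power at 0.35 SD | 55% | 42% |
| Difference detectable with 80% power | 0.49 SD | 0.55 SD |
| Completers per arm for 80% power at 0.35 SD | 102 | 130 |
| Total to enrol, dividing by 0.85 | 240 | 306 |

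**Step 4: what baseline adjustment recovers.** With equal variances at both visits, the ANCOVA variance relative to a change-score comparison is (1 - r²) / (2(1 - r)) = (1 + r)/2. This gives 0.65, 0.75 and 0.85 at r = 0.3, 0.5 and 0.7. The two-sided detectable difference of 0.55 SD of change then falls to about 0.55 × √0.65 = 0.44 at r = 0.3 and 0.55 × √0.85 = 0.51 at r = 0.7.

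**The case against.** The strongest reply is that the controlled comparison is not missing. Section 2.2 pre-specifies it over the same visits, and if the waitlist improved equally it would be expected to show no difference, next to the within-arm result. That stands, and it limits the point to rank, sizing and causal wording. It does not remove the point, because Section 2.5 names the within-arm decrease as primary and nothing makes the second hypothesis a condition for a claim of efficacy.

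Some stronger readings are tempting, but the document does not support them:

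- A reader might infer that the trial will declare TaKeTiNa effective whatever the waitlist does. No success rule is stated, so this cannot be said in either direction.
- A reader might call the 41% to 97% an inflated type I error. It is not. The stated null is no change in the intervention arm, and that null is false when patients improve for any reason. The figures are power to detect change; they show that the test does not match the claim.
- A reader might argue that the visit reveals treatment to the rater. Section 2.6 says "Raters for rater based interviews are blinded", and Section 2.8.2 places visit 3 after the last session or after two months of waiting. The visit therefore does not disclose the arm.
- A reader might infer that the trial itself prompts new care, because Section 2.10 says "People who score more than four on PHQ-9 are asked to call our outpatient care unit for an appointment". Table 1 shows the PHQ-9 only at prescreening, and nothing says that enrolled participants receive extra treatment between visits 1 and 3. Continuing usual care is stated and is enough for the argument.
- The same criticism might be extended to the cytokine and HRV hypotheses. Those are listed as further hypotheses and are not part of the defect shown here.

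**Conclusion.** Wrong as written. The primary hypothesis, the only one used for sizing, is an uncontrolled within-arm decrease that the article attributes to the therapy. A positive result would establish change and nothing about its cause.

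The size depends on how much patients improve without TaKeTiNa, which the document does not give. Over an assumed range of 0.20 to 0.50 SD of change, a therapy without effect would still give a positive primary test in 41% to 97% of trials. The reading of the text does not depend on these assumptions: Sections 1, 2.2 and 2.5 agree on the within-arm hypothesis, and Section 2.5 calls it primary.

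**What to change.** - **Section 2.2.** Make the second hypothesis the primary one: intervention minus control in HAMD-17 at visit 3, two-sided alpha 0.05, by ANCOVA with visit 1 HAMD-17 and the allocation variables sex and age as covariates. Report the change within the intervention arm descriptively. Delete the last four words of "TaKeTiNa results in a significant decrease in depression severity due to the intervention".
- **Section 2.5.** Keep N = 120 and replace the paired calculation with the power of the between-arm comparison. With 52 completers per arm, a difference of 0.35 SD of change has about 55% power one-sided or 42% two-sided, and 80% two-sided power needs about 0.55 SD of change. Add that ANCOVA improves on this, with variance 65% to 85% of the change-score analysis for an assumed correlation of 0.3 to 0.7.

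**Cost.** The change needs new wording and a new power statement. It needs no further measurements, since HAMD-17 is already scheduled at visits 1 and 3 and sex and age are already used for allocation. The downside is that the stated power becomes less favourable. Restoring 80% power at 0.35 SD on the change-score basis would take 240 (one-sided) to 306 (two-sided) participants in total, so at N = 120 the article should state openly which difference the trial can detect.

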### 2.9. Statistical Analysis

The statistical analysis will be conducted using latest version of the SPSS software available at the time of analysis. Group descriptions will be reported showing sociodemographic data as well as relevant primary and secondary outcomes. The nominal significance level will be set at α = 0.05.

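### The durability hypothesis claims no change from visit 3 to visit 4 without a comparator or an acceptable loss, and no listed hypothesis compares the arms at visit 4

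*Protocol article*

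**What the plan says.** Section 2.2 (Objectives) of the protocol article opens its list of further hypotheses with the durability claim: "The antidepressive effect of TaKeTiNa postintervention is stable over eight weeks (from visit 3 to visit 4"). It names no group, comparator, tolerated loss or decision rule.

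The two hypotheses before it are more specific. The first concerns the change within the combined intervention groups from visit 1 to visit 3. The second is a comparison of arms over the same interval: "visit 1 to visit 3) in the IG1/IG2 group compared to the CG1/CG2 group". No listed hypothesis compares the arms at visit 4.

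Section 2.9 (Statistical Analysis) gives one general criterion: "The nominal significance level will be set at α = 0.05". It does not tie this to any particular hypothesis.

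On the control arm, the Abstract says: "The waiting group receives the same therapy program after completing the follow-up period". Section 2.1 agrees. Section 2.8.2 places visit 3 at the end of therapy or of the two-month wait, and visit 4 two months later. Table 1 schedules HAMD-17 at visits 1, 3 and 4. Section 2.3 says that participants keep their usual treatment throughout.

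**The concern.** A claim of stability asserts that little or nothing changed. A significance test at 0.05 cannot confirm this, because a non-significant change may only reflect limited precision. Confirmation needs a stated limit on the loss that would still count as stable, and an interval that excludes anything larger.

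The comparator matters as well. Patients on usual treatment may improve by themselves. If intervention scores stay flat from visit 3 to visit 4 while the waitlist group catches up, the effect of TaKeTiNa has gone, yet the intervention group looks stable. Only the difference between the randomised arms shows whether the effect persists.

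At stake is a durability claim that rests on low power or on the natural course of depression, when the data for a controlled answer are already scheduled.

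**Working it through.** **Inputs.** Section 2.5 (Sample Size) gives the design as "one-tailed *t* test, difference between two dependent means, significance level 0.05, power 0.80", and states that "52 participants in the intervention group are sufficient to demonstrate a Cohen’s d of 0.35". It continues: "Anticipating a dropout rate of 15% and striving for equal group sizes, our study aims to enroll a total of 120 participants". That is 60 per arm, and 60 × 0.85 = 51 completers.

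**Step 1: reproduce the plan's figure.** The power of a paired t test comes from the noncentral t distribution with n − 1 degrees of freedom and noncentrality d·√n. For d = 0.35 and n = 52, the noncentrality is 0.35 × √52 = 2.52. At one-sided 0.05 the power is 0.801, and n = 52 is the smallest number that reaches 0.80. The stated 52 is reproduced.

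**Step 2: apply the same function to a loss between visits 3 and 4.** Losses are in units of the SD of change. The document gives no SD for the visit 3 to 4 change, so I assume that it equals the SD of the visit 1 to 3 change. The chance that a true loss is non-significant is 1 − power. Section 2.9 does not fix sidedness, so both versions are shown, with n = 51:

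| True loss | Noncentrality | Non-significant, one-sided | Non-significant, two-sided |
|---|---|---|---|
| 0.175 SD (half the planning effect) | 0.175 × √51 = 1.25 | 0.660 | 0.768 |
| 0.35 SD (all of it) | 0.35 × √51 = 2.50 | 0.206 | 0.312 |

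With n = 52 the full-loss figures are 0.199 and 0.303.

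**Step 3: vary the assumption.** If the SD of the visit 3 to 4 change is r times that of visits 1 to 3, the standardised loss is 0.35/r. At n = 52, the two-sided chance that a full loss is non-significant is 0.057 for r = 0.7 and 0.522 for r = 1.3. One-sided, it is 0.028 and 0.393.

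**Step 4: what a non-significant result leaves open.** The half-width of the two-sided 95% interval at n = 51 is t(0.975; 50)/√51 = 2.009/7.141 = 0.281 SD. An observed worsening just short of significance, 0.28 SD, has an interval from about 0 to 0.56 SD. That interval includes the whole 0.35.

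**Step 5: could the trial show stability against a margin?** Take a within-group non-inferiority test at one-sided 0.05 with no true change. A margin of 0.175 SD needs n = 204 for 80% power, and 52 patients give about 34%. A margin of 0.35 SD needs n = 52, but it tolerates loss of the whole planning effect.

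**Step 6: power of the controlled comparison.** For an unadjusted two-sample t test at visit 4 with d = 0.35 and 51 per arm, the noncentrality is 0.35 × √(51/2) = 1.77 on 100 degrees of freedom. Power is 0.417 two-sided and 0.544 one-sided. Here d is in units of the SD of the outcome being compared, which is a different SD from that in Steps 1 to 5. Adjustment for visit 1 should help, but the correlation needed to say by how much is not given.

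**The case against.** The strongest objection is that the article does not fix the analysis being criticised. A reader might infer that the durability hypothesis is a contrast within the intervention group only, that a non-significant result will be declared stability, and that the waitlist data at visit 4 will go unused. None of this is written. The hypothesis names no group, and the effect of TaKeTiNa can be read as the effect relative to control. The alpha sentence is general. Tests and margins for further hypotheses are often left to an analysis plan, and none is shown here.

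This stands as a limit on the point. The within-group reading is natural, since the first hypothesis and the sample size are both framed as change within the intervention group, but it remains a reading. The bare absence of a margin would not be a finding alone. What the article does fix is its list of hypotheses. Durability is worded as no change from visit 3 to visit 4, and the randomised comparison stops at visit 3.

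A reader might also infer that loss of the whole benefit would pass as stability. The figures do not support that: under the equal-SD assumption a full loss is detected about 69% (two-sided) to 79% (one-sided) of the time. It could be missed, and partial loss is the more serious gap. Moreover, 0.35 is given as an effect that the sample can demonstrate from visit 1 to visit 3, not as the expected benefit.

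Two further objections hold. The visit 4 comparison is itself poorly powered. It also asks whether an effect exists at visit 4, which is not the same as whether the effect was maintained since visit 3, so the fix must report both.

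**Conclusion.** The concern holds in a limited form. The durability hypothesis is a no-change claim with neither comparator nor acceptable loss, and no listed hypothesis uses the randomised comparison that is available at visit 4. If stability were concluded from a non-significant change within the intervention group, half of the planning effect could be lost unnoticed in about two thirds to three quarters of trials, and all of it in about a fifth to a third.

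These sizes rest on 51 completers, on 0.35 as the benchmark, and on equal SDs for the two change scores. The last is an assumption, and over the range in Step 3 the two-sided full-loss figure runs from about 6% to 52%. The point concerns a further hypothesis. The primary and secondary hypotheses and the sample size are not affected.

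**What to change.** Restate the hypothesis as the difference in HAMD-17 between the intervention and control groups at visit 4, adjusted for the visit 1 score. Report it with its 95% confidence interval beside the corresponding visit 3 difference. State that a non-significant change will not be read as stability.

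If the claim of stability is kept, set a margin in HAMD-17 points before visit 4 data are seen. Claim stability only if the confidence interval for the change in the between-arm difference from visit 3 to visit 4 excludes a loss larger than that margin.

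The cost is the rewording of one hypothesis; no visit, measurement or patient is added. The downside is that stability becomes harder to claim. With about 42% two-sided power at d = 0.35, the visit 4 test may well be non-significant even if an effect of that size persists, so the estimate and its interval should carry the conclusion.
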